13.1.2 Per-protocol population

This population includes parturients who are randomized into the study and consistent with all the following conditions: (1) ingested study beverage, (2) do not intake any prohibited foods, and (3) complete expected follow-ups. The primary outcome evaluation will also be performed in the per-protocol population.

13.1.3 Safety analysis population

This population includes all parturients who are randomized into the study and provided follow-up data for safety analysis. All safety data collected from participants including adverse events and laboratory test results will be evaluated and analyzed.

***13.2 General principles***

13.2.1 Numeric variables are described as mean ± standard deviation, median (interquartile range). Categorical variables are described as number of cases (percentage).

13.2.2 For each hypothesis, two-tailed tests will be used in all statistical analysis, P<0.05 will be considered statistically significant (unless otherwise indicated). For the treatment-by-covariate interaction in predefined subgroup analyses, a P<0.10 will be defined as statistically significant.

13.2.3 Statistical analysis will be performed with the SPSS 25.0 software package (IBM SPSS, Chicago, IL) and SAS 9.2 software (SAS Institute, Cary, NC).

***13.3 Patient recruitment and drop-out status***

The status of patient recruitment and drop-out will be summarized and listed. Comparison of the overall drop-out rate between the two groups will be performed with Chi-Square test.

***13.4 Demographics and baseline characteristics***

13.4.1 Demographic information and baseline characteristics will be presented.

13.4.2 The randomized groups are descriptively compared on all baseline variables using the absolute standardized differences (ASDs), defined as the absolute difference in means, mean ranks, or proportions divided by the pooled standard deviation. Baseline variables with an absolute standardized difference ≥1.96×$\sqrt{\text{(n1+n2)/(n1×n2)}}$ will be considered imbalanced and adjusted for in all analyses, using the formula published by Austin [28].

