***4.2 Sample size calculation***

In a pilot trial of our own, the rate of cesarean delivery was 8% of parturients with carbohydrate drink and 12% of those with clear liquid drink. We assumed similar rates in the present study. With the significance level set at 0.05 (two-sided) and power set at 80%, the sample size required to detect difference was 1760 parturients. Considering a drop-out rate of about 10%, we plan to enroll 2000 parturients. Sample size calculation was performed with the Stata 10.0 software (Stata Corp. LP, College Station, TX, USA).

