**5. Randomization and blinding**

***5.1 Randomization principle***

5.1.1 A biostatistician, who is independent of data management and statistical analyses, generates random numbers in a 1:1 ratio with a block size of 4 using the SAS 9.2 software (SAS Institute, Cary, NC). Randomization is stratified according to the study centers.

5.1.2 Study beverages (carbohydrate-rich beverage and commercially available low-carbohydrate beverages) are provided according to the randomization results by an anesthesiologist who does not participate in the other part of the study.

5.1.3 The results of randomization are sealed in opaque, sequentially numbered envelopes and stored at the sites of investigation.

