***13.6 Efficacy evaluation***

13.6.1 Primary endpoint:

13.6.1.1 The incidence of cesarean delivery will be calculated. Comparation between groups will be performed using Chi-Square test, with difference between groups expressed as relative risk (95% CI). The upper limit of the 95% CI of less than 1 is regarded as statistical superiority.

13.6.1.2 The interactions between treatment effect and predefined factors will be assessed separately with logistic regression models. The predefined factors include study site, age, body mass index, prepartum anemia, medical comorbidity, obstetric disease, and gynecological disease. The relative risk (and 95% CI) for each subgroup and the P values of treat-by-covariate interactions will be displayed in a forest plot.

13.6.2 Secondary endpoints:

13.6.2.1 Categorial variables (rate of forceps delivery, the rate of neonatal ward admission) between groups will be compared using Chi-Square test, continuity correction Chi-Square test, or Fisher’s exact test. Missing data will not be replaced.

13.6.2.2 Numerical variables (maternal and neonatal blood glucose after giving birth, 1- and 5-minute Apgar scores and the umbilical artery pH value) between groups will be compared using independent sample t-test or Mann-Whitney u test. Missing data will not be replaced.

13.6.2.3 Ranked data (NRS score of hunger/thirst) will be compared using Mann-Whitney u test. Missing data will not be replaced.

13.6.2.4 Relative risk (95% CI) for categorial variables, mean/median difference (95% CI) for numerical variables/ranked data will be calculated.

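### Section 13.4.2 adjusts every analysis for whatever baseline variables differ by chance, which cannot be squared with the unadjusted chi-square test and relative risk named as primary in Section 13.6.1.1

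*Protocol*

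**What the plan says.** Protocol Section 13.4.2 calls the baseline comparison descriptive but attaches a consequence to it. Any baseline variable whose absolute standardised difference reaches 1.96×√((n1+n2)/(n1×n2)) "will be considered imbalanced and adjusted for in all analyses". The variables to be screened are not given as a closed list.

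Section 13.6.1.1 states the primary analysis: "Comparation between groups will be performed using Chi-Square test, with difference between groups expressed as relative risk (95% CI"). Superiority is declared when the upper limit of that interval is below 1. Section 13.6.2 assigns chi-square, continuity-corrected chi-square, Fisher, t and Mann-Whitney tests to the secondary endpoints. The only regression named for efficacy is the logistic model in Section 13.6.1.2, and it serves the interaction tests.

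On the design, Section 5.1.1 states: "Randomization is stratified according to the study centers". Centre appears in Section 13.6 only as an interaction factor.

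**The concern.** There are two linked problems.

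First, the selection rule. Its limit is a 5% significance threshold, so under sound randomisation it picks out variables because they happen to differ between arms. Whether a variable predicts cesarean delivery plays no part. A strong predictor that is well balanced is left out, and an irrelevant variable that is imbalanced goes in.

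Second, the conflict. None of the tests listed in Sections 13.6.1.1 and 13.6.2 can take a covariate. As soon as one variable is flagged, Section 13.4.2 demands an adjusted primary analysis while Section 13.6.1.1 demands an unadjusted one. The protocol does not say which result decides superiority, or which model would give an adjusted relative risk. What is at stake is whether the trial has one primary analysis and one estimand, known before the arms are compared.

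**Working it through.** **1. The plan's own sample size.** Inputs from Section 4.2: 8% versus 12%, two-sided 0.05, power 80%. With unpooled variance, n per arm = (1.960+0.842)² × (0.12×0.88 + 0.08×0.92) / 0.04² = 879.1, so 880 per arm and 1760 in total, as stated. Pooled variance gives 882 per arm (1764). Allowing for 10% drop-out, 1760/0.9 = 1956, which the planned 2000 covers. Nothing below changes these figures.

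**2. What the limit is.** When the arms do not differ, a standardised difference has standard error of about √((n1+n2)/(n1×n2)). The limit is 1.96 times that, so each variable is flagged with probability of about 0.05 at any sample size.
- 1000 per arm: 1.96×√(2000/1,000,000) = 0.0877
- 880 per arm: 1.96×√(1760/774,400) = 0.0934

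**3. How often the conflict arises.** The protocol gives no count of baseline variables. Section 7.1 lists about 12 that can vary: age, body mass index, gestation, gravidity, comorbidities, obstetric disease, treatment, allergy, haemoglobin, hunger, thirst and glucose. With k independent variables, P(at least one flag) = 1 − 0.95^k.

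| k (assumed) | 8 | 10 | 12 | 15 | 20 |
|---|---|---|---|---|---|
| P(≥1 flag) | 34% | 40% | 46% | 54% | 64% |

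The list supports about 12. The larger values would apply only if items were split further. Correlation, such as between hunger and thirst, would lower all of these figures.

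**4. What a flag does to the estimand.** The only named regression is logistic, which yields an odds ratio. At the planning rates the relative risk is 0.08/0.12 = 0.667 and the odds ratio is (0.08/0.92)/(0.12/0.88) = 0.638. An analyst who adjusted with the model at hand would report a different quantity from the one in the superiority rule.

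**5. What it does to error rate, verdict and power.** The simulation used 1000 per arm, 10 independent normal covariates of which one is prognostic, and 3000 runs per setting. The log-odds intercept was −2.1 (a 10.9% rate at the covariate mean). When a variable was flagged, a logistic model stood in for the unnamed adjusted analysis. The columns from chi-square to prespecified give the proportion of trials reaching significance.

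| Treatment odds ratio | Prognostic log-odds per SD | Any flag | Chi-square | Section 13.4.2 rule | Prespecified adjustment | Rule and chi-square disagree |
|---|---|---|---|---|---|---|
| 1.00 | 0.4 | 0.402 | 0.046 | 0.046 | 0.044 | 0.002 |
| 1.00 | 0.8 | 0.408 | 0.049 | 0.047 | 0.048 | 0.008 |
| 0.64 | 0.4 | 0.412 | 0.813 | 0.813 | 0.816 | 0.008 |
| 0.64 | 0.8 | 0.405 | 0.831 | 0.834 | 0.857 | 0.014 |

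The simulation standard error at 0.05 is √(0.05×0.95/3000) = 0.004. The prognostic covariate was flagged in about 5% of trials, no more often than any other.

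**6. Centre.** With 1:1 blocks of 4 within centre, the arms differ by at most 2 women per centre at randomisation. For nine centres of equal size (an assumption), the standardised difference is at most about (2/1000)/√(0.111×0.889) = 0.006, far below 0.088. The rule would almost never select the stratification factor.

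**The case against.** The strongest defence is that the rule is written in advance, is mechanical and looks only at baseline data. It is not selection driven by outcome. A reader might infer that the nominal 5% error rate no longer holds, or that the superiority verdict hangs on chance imbalance. The documents do not support either inference. The simulated type I error under the rule was 0.046 to 0.047, and the verdict differed from that of the chi-square test in only 0.2% to 1.4% of trials. The 46% figure is the chance that the analysis changes form, not that the conclusion changes.

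A reader might also infer that every flag must be a chance finding. That is too absolute here. Section 3.4 removes women after randomisation if they take no study beverage or lack the primary outcome. Treatment is open-label, and allocation uses fixed blocks of 4 with envelopes held at the sites. Real imbalance in the analysed set is possible. Automatic adjustment for whatever crosses a 5% limit is still a poor remedy for it.

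Section 13.4.2 can further be read as a conditional instruction: the tests in Section 13.6 are the default, and the adjusted result governs after a flag. The missing model name could then be left to a statistical analysis plan, which was not available for this review. This softens the conflict but does not remove it. The superiority rule is attached to the unadjusted comparison, and a later plan that follows one section departs from the other.

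Finally, an unadjusted chi-square test is valid under randomisation, and the precision forgone is modest. That stands.

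**Conclusion.** The point holds as a conflict between two stated instructions and as a poor selection rule. Once any variable is flagged, Sections 13.4.2 and 13.6.1.1 cannot both be followed. With about 12 baseline items this happens in up to about 46% of trials if the items are independent, and less often if they are correlated.

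The harm is limited. Type I error is not materially inflated and the verdict would seldom change. What is lost is a determined primary analysis and estimand, together with some precision: in the strong-covariate setting, power was 0.834 under the rule against 0.857 with prespecified adjustment. The gain in the weaker setting was negligible (0.813 against 0.816). These simulation results assume sound randomisation, independent covariates and a logistic model in place of the unnamed one. Interval coverage for an adjusted relative risk was not examined. The sample size is unaffected. This should be fixed, but it does not undermine the trial.

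**What to change.** Keep the standardised differences as description only and delete the requirement to adjust all analyses for flagged variables. Fix one primary analysis before unblinding.

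- **Preferred:** name a model that gives the relative risk, for example modified Poisson regression with robust standard errors. Include centre and a short list of prognostic baseline factors fixed in advance, whatever balance is observed. Attach the superiority rule to that estimate and report the unadjusted relative risk as a sensitivity analysis. Age, body mass index and gestational age are already collected and are candidates, but the protocol gives no evidence of how prognostic they are, so the choice needs a clinical rationale.
- **Minimum:** keep the chi-square test and unadjusted relative risk as primary, and make any imbalance-based adjustment a sensitivity analysis with a named model.

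Apply the same decision to the secondary endpoints in Section 13.6.2. The cost is a change of wording and slightly more programming, with no new data and no change to the sample size.

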***13.5 Intrapartum variables***

Numeric variables will be analyzed using the independent-samples t test or Mann-Whitney U test; categorical variables will be analyzed using the chi square test, continuity correction chi square test or Fisher exact test. Missing data will not be replaced.

***13.6 Efficacy evaluation***

13.6.1 Primary endpoint:

13.6.1.1 The incidence of cesarean delivery will be calculated. Comparation between groups will be performed using Chi-Square test, with difference between groups expressed as relative risk (95% CI). The upper limit of the 95% CI of less than 1 is regarded as statistical superiority.

13.6.1.2 The interactions between treatment effect and predefined factors will be assessed separately with logistic regression models. The predefined factors include study site, age, body mass index, prepartum anemia, medical comorbidity, obstetric disease, and gynecological disease. The relative risk (and 95% CI) for each subgroup and the P values of treat-by-covariate interactions will be displayed in a forest plot.

13.6.2 Secondary endpoints:

13.6.2.1 Categorial variables (rate of forceps delivery, the rate of neonatal ward admission) between groups will be compared using Chi-Square test, continuity correction Chi-Square test, or Fisher’s exact test. Missing data will not be replaced.

13.6.2.2 Numerical variables (maternal and neonatal blood glucose after giving birth, 1- and 5-minute Apgar scores and the umbilical artery pH value) between groups will be compared using independent sample t-test or Mann-Whitney u test. Missing data will not be replaced.

13.6.2.3 Ranked data (NRS score of hunger/thirst) will be compared using Mann-Whitney u test. Missing data will not be replaced.

13.6.2.4 Relative risk (95% CI) for categorial variables, mean/median difference (95% CI) for numerical variables/ranked data will be calculated.

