***4.3 Study center***

This trial will be conducted in 9 obstetric-led maternity units in tertiary hospitals in China. Nine hospitals expected to participate in this study are Peking University First hospital; Woman's Hospital of Nanjing Medical University; Tangshan Maternity and Child Health Care Hospital; Foshan Maternal and Child Health Hospital; Gansu Provincial Maternity and Child Care Hospital; Urumqi Women and Child Health Care Hospital; Linyi people's hospital; Anhui Women and Child Health Care Hospital; Women's Hospital of Zhejiang University.

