**8. Outcome assessment**

***8.1 Primary outcomes***

The rate of cesarean delivery.

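### The primary test of caesarean delivery ignores centre, the factor used to stratify randomisation; if centre rates differ, the interval is slightly too wide (minor)

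*Protocol*

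**What the plan says.** Protocol 5.1.1 describes how the biostatistician "generates random numbers in a 1:1 ratio with a block size of 4" and adds: "Randomization is stratified according to the study centers". Section 4.3 gives the number of strata: "This trial will be conducted in 9 obstetric-led maternity units in tertiary hospitals in China". Centre is the only stratification factor named.

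The primary outcome (8.1) is binary: "The rate of cesarean delivery". For it, 13.6.1.1 states: "Comparation between groups will be performed using Chi-Square test". The effect is reported as a relative risk with a 95% CI, and the decision rule is: "The upper limit of the 95% CI of less than 1 is regarded as statistical superiority". No centre term or stratified method is attached to this comparison.

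Study site appears in the analysis only in 13.6.1.2, as one of seven factors whose interaction with treatment is examined in separate logistic models. Section 13.4.2 provides for covariate adjustment, but only for baseline variables whose standardised difference passes a stated threshold.

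**The concern.** Blocking within centre makes the arms nearly equal in every centre, so differences in caesarean rate between hospitals cannot contribute materially to the difference between arms. A pooled chi-square test and crude relative risk do not use this. Their variance is built on the overall rate and so includes the between-centre spread as if it were random error. The result is an interval somewhat wider than the design warrants and a test somewhat below its nominal level.

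This only matters if centres differ. There is some reason to expect it: 6.3.2 leaves caesarean delivery to the attending obstetricians and midwives in nine hospitals, and the protocol itself chose centre as the variable to stratify on. At stake is a little precision and power on the single primary endpoint of a trial designed at 80% power.

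The choice cannot be called open until a statistical analysis plan is written, because the protocol names the unstratified test.

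**Working it through.** **Inputs from the protocol.** Rates (4.2): "the rate of cesarean delivery was 8% of parturients with carbohydrate drink and 12% of those with clear liquid drink". Error rates (4.2): "With the significance level set at 0.05 (two-sided) and power set at 80"%. Stated size: 1760, enrolled 2000 after about 10% drop-out. Nine centres, 1:1 allocation, blocks of 4.

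**The plan's own figure.** With unpooled variance, n per arm = (1.96 + 0.842)² × (0.08×0.92 + 0.12×0.88) / 0.04² = 879.07, so 880 per arm and 1760 in total, as stated. The pooled-variance formula gives 882 per arm, or 1764. Drop-out: 1760/0.9 = 1956, rounded up to 2000. The sample size is sound and is not in question.

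**Would 13.4.2 bring centre in?** At 1000 per arm the threshold is 1.96 × √(2000/1,000,000) = 0.088. With blocks of 4, an unfinished block can leave a centre at most 2 participants out of balance, a difference in proportions of 0.002. For a centre holding one ninth of participants the SD is √(0.111×0.889) = 0.314, so the standardised difference is at most about 0.006. Centre would not be expected to meet the rule.

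**Variance with and without centre.** Let m be the mean rate and B the variance of the nine centre rates (equal-sized centres). The pooled variance is m(1−m). The within-centre variance is m(1−m) − B.

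- Ratio R = 1 − B/[m(1−m)]
- Standard error overstated by 1/√R − 1
- Actual two-sided type I error = 2 × [1 − Φ(1.96/√R)]

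The protocol gives no centre rates. The spreads below are assumptions: nine evenly spaced rates with mean m = 0.10, the midpoint of 8% and 12%, so m(1−m) = 0.09. For nine evenly spaced values with step s, B = s² × 80/12.

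| Centre rates | B | R | SE overstated | Type I error |
|---|---|---|---|---|
| all 10% | 0 | 1 | 0% | 5.0% |
| 8–12% | 0.000167 | 0.9981 | 0.09% | 4.98% |
| 4–16% | 0.00150 | 0.9833 | 0.84% | 4.81% |
| 2–18% | 0.00267 | 0.9704 | 1.52% | 4.66% |

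**Power.** Scale the centre rates to 12% and 8% on average, with a constant relative risk of 2/3. Power ≈ Φ[(0.04 − 1.96 × s0)/sw], where s0 is the standard error used by the test (pooled or within-centre) and sw is the true standard error.

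Example for 4–16%, 1000 per arm:

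- Crude s0 = √(2×0.09/1000) = 0.01342
- Stratified s0 = √(2×0.0885/1000) = 0.01330
- sw = √[(0.10344 + 0.07264)/1000] = 0.01327
- Power is 84.9% crude and 85.3% stratified

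| Centre rates | 1000 per arm, crude / stratified | 880 per arm, crude / stratified |
|---|---|---|
| 8–12% | 84.7% / 84.8% | 79.9% / 80.0% |
| 4–16% | 84.9% / 85.3% | 80.1% / 80.6% |
| 2–18% | 85.1% / 85.8% | 80.3% / 81.1% |

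Unrounded, the losses are about 0.05, 0.4–0.5 and 0.7–0.8 points.

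**Check by simulation** (200,000 runs, nine equal centres, 999 per arm), crude against Cochran-Mantel-Haenszel. Type I error: 5.0% vs 5.0% (8–12%), 4.8% vs 5.0% (4–16%), 4.7% vs 5.1% (2–18%). Power: 84.9% vs 84.9%, 85.1% vs 85.5%, 85.3% vs 86.0%. The simulation agrees with the formulas.

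**Bias.** With equal arms in every centre, the crude and Mantel-Haenszel relative risks are the same number. Only the width of the interval changes.

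**The case against.** The strongest defence is that an unstratified chi-square test after stratified randomisation is valid. It errs only on the conservative side and needs no assumption about centre effects. That stands.

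The size is also limited. Section 6.3.2 says caesarean delivery follows Chinese guidelines. All units are in tertiary hospitals (4.3), and participants are a fairly uniform group: primiparae with a single cephalic pregnancy beyond 37 weeks, aged 18 to 34, without diabetes. Centre rates may be close. The rounding up to 2000 helps too: with 10% lost, 900 per arm remain and power is 80.8%, against 79.9% at 880. That covers a loss of this order. These points are fair and are why this is a minor point; they are not a reason to keep an analysis that leaves out the one factor the design controls.

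Three stronger readings are tempting, and the document does not support them.

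- A reader might take it as fact that the standard error is overstated. It is so only if centre rates differ, and no centre rates are given. Larger effects need wider spreads: a skewed set running from 1% to 30% with mean 10% gives a 5.2% overstatement and about 2 points of power, but nothing in the protocol points to that.
- A reader might infer two competing success criteria, chi-square P<0.05 and an upper confidence limit below 1. Section 13.6.1.1 states only the second. The P<0.05 convention in 13.2.2 applies unless otherwise indicated, and 13.6.1.1 does indicate otherwise. The two would disagree in only about 0.2% of trials at the design rates.
- A reader might extend the point to the secondary binary outcomes. Section 13.6.2.1 already allows for exact or continuity-corrected tests there, and no calculation here covers sparse events across nine strata.

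**Conclusion.** The mismatch between design and primary analysis is certain from the text; its consequence is conditional and small. If caesarean rates differ between centres, the crude interval is slightly too wide and the test slightly conservative. Across the assumed spreads from 8–12% to 2–18%, the standard error is overstated by about 0.1% to 1.5%, the actual type I error is 4.98% to 4.7%, and less than 1 point of power is lost. These figures assume a mean rate of 10%, equal-sized centres, even spacing and a constant relative risk.

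Nothing here threatens the validity of the trial. The case for changing the analysis is that it costs nothing and recovers what the stratification was meant to buy. A statistical analysis plan, if one exists, may already do this; that cannot be checked here.

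**What to change.** In 13.6.1.1, make the primary analysis the Cochran-Mantel-Haenszel test stratified by study centre, with the Mantel-Haenszel common relative risk and its 95% CI. Apply the existing superiority rule, upper limit below 1, to that interval. Keep the crude chi-square test and crude relative risk as a sensitivity analysis.

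Sparse strata are not an obstacle for this outcome: with equal centres, 2000/9 ≈ 222 participants per centre at 10% gives about 22 caesareans each.

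The cost is one sentence, to be written before the database is locked and unblinded (section 11). It needs no extra data or participants, no change to the sample size, and can be run in the SAS and SPSS packages named in 13.2.3.

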***6.2 Study intervention***

6.2.1 Study intervention will be administered during epidural labor analgesia.

6.2.2 Parturients in the carbohydrate-rich group are provided with an oral carbohydrate-rich solution [Outfast®: 285 mOsm/kg, 14.1% carbohydrate (maltodextrin 100g/L, fructose 23.9g/L, glucose 16.9g/L), Na^+^ 2.0 mmol/L, K^+^ 4.9 mmol/L, 0.58 kcal/ml; Yichang Humanwell Pharmaceutical Co, Ltd, Hubei, China] and are advised to drink as will during labor.

6.2.3 Parturients in the low-carbohydrate group are advised to drink commercially available low-carbohydrate beverages as will (Pocarisweat®: 0.26 kcal/ml, Otsuka Pharmaceutical Co. Ltd, Tokyo, Japan; Gatorade®, 0.24 kcal/ml, PepsiCo, Chicago, IL, USA; or Mizone®: 0.21 kcal/ml, Danone, Guangzhou, Guangdong, China).

6.2.4 All participants have free access to water, but solid foods are not permitted.

6.2.5 Dietary intake prior to labor analgesia and after the third stage of labor are not interfered.

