**7. Data collection**

***7.1 Prepartum data***

7.1.1 Demographic data, including gender, date of birth, and body mass index.

7.1.2 Diagnosis and medical history, including duration of gestation, gravidity, prepartum comorbidities, comorbid obstetric disease, medical treatment, history of allergy to food and drugs, and prepartum hemoglobin

7.1.3 Subjective discomfort (degree of hunger and thirst) is assessed using the Numeric Rating Scale (NRS, an 11-point scale where 0 indicated no hunger/thirst and 10 indicated the most severe hunger/thirst) at the initiation of epidural labor analgesia.

7.1.4 Maternal blood glucose level is tested using a blood glucose monitor (Accu-Chek®, Roche, Germany) at the initiation of epidural labor analgesia.

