***8.2 Secondary outcomes***

8.2.1 Duration of labor.

8.2.2 Rate of forceps delivery.

8.2.3 The NRS score of hunger/thirst.

8.2.4 Maternal blood glucose after giving birth.

8.2.5 1- and 5-minute Apgar scores.

8.2.6 The umbilical artery pH value after birth.

8.2.7 Neonatal blood glucose after birth.

8.2.8 The rate of neonatal ward admission.

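### Maternal glucose and hunger/thirst are analysed without each woman's own baseline value or centre, which costs some precision on secondary outcomes but causes no bias

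*Protocol*

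**What the plan says.** **Baseline.** Protocol 7.1.4: "Maternal blood glucose level is tested using a blood glucose monitor", at the start of epidural analgesia. Protocol 7.1.3, at the same moment: "Subjective discomfort (degree of hunger and thirst) is assessed using the Numeric Rating Scale", an 11-point scale. Protocol 6.2.1: "Study intervention will be administered during epidural labor analgesia". I therefore read the values taken at its start as pre-drink baselines.

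**Outcomes.** Protocol 8.2.4 lists "Maternal blood glucose after giving birth" and 8.2.3 lists "The NRS score of hunger/thirst". The second has no time point, either there or in sections 7.2 and 7.3.

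**Tests.** Under 13.6.2.2, numerical variables including maternal glucose "between groups will be compared using independent sample t-test or Mann-Whitney u test". Under 13.6.2.3, "Ranked data (NRS score of hunger/thirst) will be compared using Mann-Whitney u test". Neither has a baseline or centre term. Section 13.6.2.4 adds mean or median differences with 95% confidence intervals.

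**Adjustment rule.** Under 13.4.2, baseline variables whose absolute standardised difference reaches 1.96 × √((n1+n2)/(n1×n2)) "will be considered imbalanced and adjusted for in all analyses". No adjusted model is named.

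**Randomisation.** Section 5.1.1 stratifies by study centre; section 4.3 lists nine.

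**The concern.** When an outcome has also been measured before treatment, that earlier value is usually among its best predictors. A two-sample test leaves the variation it explains in the error term, so the confidence interval is wider than the data require. Centre, the randomisation stratum, is left out in the same way.

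These outcomes bear on whether the richer drink changes maternal glucose and comfort. The protocol does not leave the method open for a later document: it names unadjusted tests. The conditional rule in 13.4.2 does not fill the gap, because it selects covariates by whether they happen to be imbalanced and not by whether they predict the outcome.

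At stake is the width of the intervals for maternal glucose and, once its assessment time is stated, for hunger/thirst. Neonatal glucose, Apgar scores and umbilical artery pH have no baseline value, so baseline adjustment does not arise for them.

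**Working it through.** **1. The plan's own figure.** Section 4.2 gives 8% versus 12%, two-sided 0.05 and 80% power. With unpooled variance, n per arm = (0.12×0.88 + 0.08×0.92) × (1.960 + 0.842)² / 0.04² = 0.1792 × 7.849 / 0.0016 ≈ 879.1, rounded up to 880, so 1760 in total. This matches the protocol. (Pooled variance gives 882 per arm, 1764.) Then 1760/0.9 = 1956, rounded up to 2000. The protocol gives no SD, power or baseline-outcome correlation for glucose or hunger/thirst.

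**2. What the unadjusted test already delivers.** With 1000 per arm, the difference detectable with 80% power is (1.960 + 0.842) × √(2/1000) = 0.125 SD. With 880 per arm it is 0.134 SD.

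**3. How often 13.4.2 triggers.** The threshold is 1.96 × √(2000/1,000,000) = 0.088 SD at 1000 per arm and 0.093 SD at 880 per arm. Under randomisation the standardised difference has standard error close to √((n1+n2)/(n1×n2)), so the rule is a two-sided 5% test. A given variable crosses it about 5% of the time and is left unadjusted about 95% of the time.

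**4. What adjustment would add.** For a linear model, variance of the adjusted difference = (1 − r²) × unadjusted variance. The correlation r is an assumption. At N = 2000:

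| Assumed r | Variance reduction (r²) | CI width ratio √(1−r²) | Unadjusted N needed, 2000/(1−r²) | Detectable difference (SD) | Power at 0.125 SD |
|---|---|---|---|---|---|
| 0.1 | 1% | 0.995 | 2020 | 0.125 | 80% |
| 0.2 | 4% | 0.980 | 2083 | 0.123 | 82% |
| 0.3 | 9% | 0.954 | 2198 | 0.120 | 84% |
| 0.4 | 16% | 0.917 | 2381 | 0.115 | 86% |
| 0.5 | 25% | 0.866 | 2667 | 0.109 | 90% |
| 0.6 | 36% | 0.800 | 3125 | 0.100 | 94% |

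The formula applies directly to mean glucose. For Mann-Whitney or proportional-odds analyses of hunger/thirst it is only a rough guide. The effect of adding centre is not quantified here.

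**5. How much of the gain 13.4.2 recovers.** A simulation of 4000 trials at 1000 per arm with normal data compared three policies:

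| r | Rule triggered | Variance, always adjust (unadjusted = 1) | Variance, 13.4.2 rule |
|---|---|---|---|
| 0.3 | 5.2% | 0.92 | 0.98 |
| 0.5 | 4.7% | 0.77 | 0.94 |

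The rule captures about a quarter of the available gain: 0.02/0.08 at r = 0.3 and 0.06/0.23 at r = 0.5.

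**The case against.** The strongest reply is that nothing here is invalid. The t and Mann-Whitney tests are sound under randomisation, and a trial sized for a binary primary outcome already detects about 0.125 SD on a continuous secondary outcome. Adjustment moves that to 0.120 SD at r = 0.3 and 0.100 SD at r = 0.6. It is hard to name a conclusion that would change. All of this stands, and it limits the weight of the point.

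The correlation may also be low. Labour of unstated length, drinking at will and an intravenous infusion lie between the two glucose readings. Unrestricted diet before analgesia (6.2.5) makes women start at different levels, but that matters only as far as the differences persist to delivery. This stands too, and is why the range starts at 0.1.

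A reader might infer that sharper estimates of mean glucose would sharpen the glucose safety assessment. The protocol does not support that: maternal hypoglycaemia and hyperglycaemia are defined by thresholds (9.3.3, 9.3.4), and adverse event rates are compared under 13.6.3.3. A reader might also infer that the hunger/thirst test compares post-intervention scores. That is plausible for an outcome, but the only assessment time the protocol states is the start of analgesia.

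Finally, 13.4.2 does protect against a notable chance imbalance. It does not recover most of the precision, and it names no model to replace the Mann-Whitney test when it triggers.

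**Conclusion.** The point holds as an avoidable loss of precision on secondary outcomes. It is clearest for maternal glucose after birth, and extends to hunger/thirst once a post-baseline time is stated. The size is a variance reduction of r² forgone: 1% to 36% for an assumed r of 0.1 to 0.6, small below 0.3 and material from about 0.4 to 0.5. The result rests on that assumed range, on a linear model, and on the values at the start of analgesia preceding the first drink.

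It should not be read as a claim of bias, of an invalid test, or of any effect on the caesarean comparison or the sample size; the document supports none of these. It is still worth acting on, because the method is stated, the baseline is already collected, and the conditional rule leaves the adjustment to chance. If r is near zero, almost nothing is lost by adjusting: one degree of freedom for the baseline and eight for nine centres, out of about 2000 women.

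**What to change.** In Protocol 13.6.2, and in any SAP:

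- **Maternal glucose after birth:** ANCOVA with treatment, baseline glucose (7.1.4) and centre, reported as an adjusted mean difference with 95% CI.
- **Hunger and thirst, each separately:** a proportional-odds or rank-based ANCOVA model with treatment, baseline score (7.1.3) and centre. State the post-baseline assessment time in sections 7 and 8.2.3. State also the effect measure, since a proportional-odds model gives an odds ratio and not the median difference promised in 13.6.2.4.
- Say that these covariates enter regardless of observed imbalance, so that 13.4.2 does not decide the matter for these outcomes.
- Keep the t and Mann-Whitney tests as sensitivity analyses. Missing data are not replaced under 13.6.2, so a woman without a baseline value would drop out of the adjusted model but remain in these.

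The cost is a few sentences. Both glucose readings and the baseline scores are already scheduled, and no extra participants are needed. The hunger/thirst part also needs the later assessment time to be fixed, which the unadjusted test needs as well.
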